### Plans to give access to the full protocol, participant-level data, and statistical code {31c}

De-identified research data will be stored and accessible to the principal investigator (PI) and available to those interested upon reasonable request.

### Oversight and monitoring

#### Composition of the coordinating center and trial steering committee {5d}

This trial does not include a coordinating center or trial steering committee. The sole responsibility for coordination falls on the core study team. Automated data collection and recorded database actions ensure data integrity. Any major changes to the study protocol will be reviewed and verified by the Research Ethics Committee. A physician with expertise in audiology and clinical experience will be available for consultation during the trial.

#### Composition of the data monitoring committee, its role, and reporting structure {21a}

A data monitoring committee is not required as all participants are self-referred and data is coded directly into a system that cannot be adjusted with all actions being logged. Weekly contact with research team members will be maintained to monitor for adverse events, which will be reported to the principal investigator. In case of adverse events, the participant will be interviewed by a clinically experienced team member and informed about relevant community services.

#### Adverse event reporting and harms {22}

Participants will be instructed that during the trial, they are to report any adverse effects to the trial administrator. A clinician from the research team will investigate any reported incidents and will direct participants to appropriate care if needed. All data on adverse events will be included in the publication of the main outcome results.

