## Methods: participants, interventions, and outcomes

### Study setting {9}

This study will be conducted completely remotely. All screening and outcome questionnaires will be completed online and intake, and post-treatment interviews will be done on the phone. The intervention is provided via a web-based platform and is mobile device friendly. All participants who speak Lithuanian regardless of their place of residence will be considered for participation in the trial as long as they are available for an interview over the phone. The participant flowchart is shown in Fig. 1.

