##### Internet-delivered cognitive behavioral therapy for tinnitus (ICBT)

The ICBT intervention for the experimental group will start after group allocation. The ICBT is based on a self-help program created by Andersson and colleagues and is designed to address the physical, emotional, and problematic effects of tinnitus for habituation [35]. The program includes key audiological principles and has been modified previously to an interactive e-learning format for better engagement [10]. The 16 recommended modules and 5 optional modules can be tailored to individual needs and are released weekly over an 8-week period. Participants are encouraged to engage with the modules and practice the suggested techniques daily. The program is comprehensive, offering a range of CBT techniques, and can be accessed online, downloaded, or printed. It includes information, videos, quizzes, diagrams, worksheets, and solutions for common problems. Participants can also use a secure messaging system to ask questions and receive feedback from their assigned program therapists.

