##### Internet-delivered mindfulness-based tinnitus stress reduction.

The i-MBTSR course consists of 8 online lessons held weekly, which include videos, audio recordings, and written content covering tinnitus education, mindfulness, gentle yoga, and guided meditations [25]. Participants are required to do 30 min of daily meditation and attend a daylong practice session between the 6th and 7th week to enhance their mindfulness skills. The course aims to provide in-depth tinnitus education, reduce tinnitus-related anxiety, and teach meditation skills to help participants view tinnitus as a normal part of their sensory experience, reducing its bothersome effects. Just like the ICBT participants, individuals assigned to iMBTSR group will also have the ability to use the same secure messaging system to ask questions and receive feedback from their assigned program therapists.

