#### Criteria for discontinuing or modifying allocated interventions {11b}

Participants will be instructed to notify the research staff in the event of a decline in their condition. Within 24 h, a trained clinical psychologist will conduct a thorough clinical assessment via telephonic interview. Based on the results of the evaluation, the participant may be referred for hospitalization or other necessary medical services.

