### Participant timeline {13}

Participant timeline is presented in Table 1.

**Table 1 Tab1:** Schedule of enrollment, interventions, and assessments

Assessment/activity	Online screening/baseline	Telephone interview	Post-randomization			Follow-up	
	* − t*1	*t*0	*t*1–*t*8 (weekly)	*t*1–*t*8 (biweekly)	*t*9 (post)	*f*1	*f*2
Informed consent	X						
Demographic data	X						
iCBT			X				
iMBTSR			X				
THI-S				X			
THI	X				X	X	X
PHQ-9	X				X	X	X
GAD-7	X				X	X	X
ISI	X				X	X	X
THS	X				X		
MAAS	X				X	X	X
TCQ	X				X	X	X
BFI-10	X						
Eligibility criteria		X					
Treatment expectancy		X					
Treatment engagement			X				

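### Adverse events rest on spontaneous reports and a loosely defined weekly contact, with no standard question on any scheduled form, so capture may differ between the active arms and the waiting list up to week 8

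*Protocol article*

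**What the plan says.** The protocol article describes these routes by which harms reach the team.

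- **Adverse event reporting and harms {22}:** the route stated here is spontaneous: "Participants will be instructed that during the trial, they are to report any adverse effects to the trial administrator". Reported incidents are then looked into by a clinician. The main results paper is to carry all adverse-event data.
- **Criteria for discontinuing or modifying allocated interventions {11b}:** this route is also started by the participant: "Participants will be instructed to notify the research staff in the event of a decline in their condition".
- **Composition of the data monitoring committee {21a}:** "Weekly contact with research team members will be maintained to monitor for adverse events, which will be reported to the principal investigator". The frequency and the purpose are fixed. The arms, the mode of contact, what is asked and how long it continues are not stated.

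None of these three is limited to an arm.

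The intervention sections describe a further line of contact for treated participants only. For ICBT: "Participants can also use a secure messaging system to ask questions and receive feedback from their assigned program therapists". For the mindfulness programme: "individuals assigned to iMBTSR group will also have the ability to use the same secure messaging system". No such channel is described for the waiting list, whose members choose one of the two interventions after 8 weeks.

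Table 1, titled "Schedule of enrollment, interventions, and assessments", has neither an adverse-event row nor a row for the weekly contact.

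**The concern.** Spontaneous reporting tends to rise with how often a participant speaks to someone in the trial. Here participants and staff know the allocation, and the two treated arms have an assigned therapist to write to while the waiting list, as described, does not. If an unwanted effect mentioned to a therapist is logged, and the same effect on the waiting list is never asked about, the published counts would make the programmes look less safe than waiting for no real reason. Without a standard question, events could also be under-counted in every arm.

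After week 8 there is no scheduled point at which anyone is asked, although follow-up runs to 12 months. The article describes no steering committee, no data monitoring committee and no auditing. The weekly contact is thus the main active harms safeguard it states, and its coverage should be clear.

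**Working it through.** **1. Is there a figure to reproduce?** No. The document gives no expected adverse-event rate and no harms comparison. The only usable number is the arm size. The Sample size section has 42 in total plus 25%: 42 × 1.25 = 52.5, and 52.5 / 3 = 17.5, which matches its figure of about 18 per arm.

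**2. The sections side by side.**

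| Route | Who starts it | Arms | Shown in Table 1? |
|---|---|---|---|
| Report to the administrator {22} | Participant | Not limited | No |
| Report of a decline {11b} | Participant | Not limited | No |
| Weekly contact {21a} | Reads as active monitoring | Not limited, not specified | No |
| Therapist messaging {11a} | Participant | ICBT and iMBTSR only | Not as a harms item |

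Table 1 has 16 rows: consent, demographics, the two interventions, THI-S, THI, PHQ-9, GAD-7, ISI, THS, MAAS, TCQ, BFI-10, eligibility, expectancy and engagement. No row asks about adverse events at week 8 or at either follow-up.

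The Study setting section says "intake, and post-treatment interviews will be done on the phone", whereas Table 1 has a telephone interview only at t0. That is a clerical mismatch. The content of the interview is not stated, so it carries no weight here.

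**3. What unequal capture could do (illustration, assumed values only).** Let the true event risk p be the same in every arm, and let capture be cA in an active arm and cW on the waiting list. Then

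- recorded risk: pA = p × cA and pW = p × cW
- spurious risk difference: p × (cA − cW)
- standard error: √[pA(1 − pA)/18 + pW(1 − pW)/18]

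With cA = 90% throughout:

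| True risk p | cW | Spurious difference | SE | Expected recorded events per 18, active v waiting |
|---|---|---|---|---|
| 10% | 70% | 2 points | 9.0 | 1.6 v 1.3 |
| 10% | 50% | 4 points | 8.5 | 1.6 v 0.9 |
| 10% | 30% | 6 points | 7.9 | 1.6 v 0.5 |
| 20% | 70% | 4 points | 12.2 | 3.2 v 2.5 |
| 20% | 50% | 8 points | 11.5 | 3.2 v 1.8 |
| 20% | 30% | 12 points | 10.6 | 3.2 v 1.1 |
| 30% | 70% | 6 points | 14.2 | 4.9 v 3.8 |
| 30% | 50% | 12 points | 13.4 | 4.9 v 2.7 |
| 30% | 30% | 18 points | 12.4 | 4.9 v 1.6 |

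The last row in full: 0.30 × (0.90 − 0.30) = 0.18, with SE = √[(0.27 × 0.73 + 0.09 × 0.91)/18] = 0.124.

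If cA = cW the difference is 0. The ratio of recorded risks is always cA/cW, so quoting a ratio only hands back the assumption. No capture rate comes from the document.

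**4. Where the risk applies.** ICBT and iMBTSR share the same messaging system, so the text gives no reason for unequal capture between them. After week 8 the waiting list takes up an intervention, so no untreated comparison remains. The concern about unequal ascertainment is therefore confined to active arms versus waiting list, up to week 8.

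**The case against.** A reader might infer that the harms comparison is biased, that the weekly contact is unscheduled, or that nothing is collected during follow-up. The document supports none of these as stated.

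- The contact is fixed as weekly and is expressly for adverse-event monitoring. Like the two reporting instructions, it is restricted to no arm. If it is the same everywhere, the feared difference disappears.
- Messaging is described as a means of putting questions to a therapist and getting feedback, not as a harms route. That events raised there would be logged is an inference.
- The instruction to report holds for the duration of the trial, which can be read to include follow-up.
- The data collection section lists only pre-randomisation, termination and the two follow-ups. It cannot be an exhaustive limit, because THI-S is scheduled at weeks 2, 4 and 6.
- No between-arm harms test is planned. The article promises only to publish the data.
- THI, PHQ-9, GAD-7 and ISI are measured at week 8 and at both follow-ups without distinction by arm, so symptom worsening is already captured on a common schedule.
- This is a condensed article. A contact script or adverse-event form may exist in the full protocol.

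All of this stands, and it removes any claim of demonstrated bias. It does not remove the point. The article prints its own assessment schedule and names its own collection method. That method depends mainly on participants volunteering information in an open-label trial, and the schedule contains no solicited item. Even without a formal test, harms data from a three-arm trial will be read by arm. The symptom scales show worsening on their own items but would miss other unwanted effects.

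**Conclusion.** The concern holds in a limited form. Adverse-event capture is at risk of differing between the active arms and the waiting list up to week 8, and capture after week 8 has no scheduled point and may rest on spontaneous report. The risk comes from three stated features together: open-label allocation, therapist messaging described for two arms only, and no standard adverse-event question on any form.

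The size is unknown. The range of 2 to 18 percentage points rests wholly on assumed true risks of 10 to 30% and capture of 90% against 70, 50 or 30%. With 18 per arm the standard errors are 8 to 14 points, so such a difference would usually sit within chance variation. Equal capture in all arms gives zero, and the article does not say which case applies. The primary THI analysis and the ICBT versus iMBTSR comparison are not affected. The point deserves action because a better method is available at almost no cost.

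**What to change.** 1. Add one identical compulsory question to the online questionnaires already scheduled at week 8, 3 months and 12 months: any unwanted effect or worsening since the last form, with its start date. Add it to the THI-S forms at weeks 2, 4 and 6 as well if all three arms receive them. The article does not say whether the waiting list does.
2. Add the matching row to Table 1.
3. State in {21a} that the weekly contact is the same in all three arms, how adverse events are asked about, and when it ends.
4. Tabulate solicited reports by arm up to week 8, with the number answering as denominator. List spontaneous and therapist-relayed reports separately.
5. Optionally, give the number per arm whose THI rose by at least 7 points at week 8. Label it a descriptive count, because the Sample size section uses 7 points as a group-level margin and not as a threshold for individual deterioration.

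As a tidy-up, align the post-treatment telephone interview with Table 1.

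The cost is one question on existing forms, one row and one extra table, with no extra visits. The downside is that more minor events will be recorded.

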#### Frequency and plans for auditing trial conduct {23}

Sponsoring institution does not have a dedicated trial auditing department; therefore, no auditing is planned for this trial. Principal investigators will meet weekly during the study to review trial progress. Investigators are obliged to and will inform the research ethics committee in case of any major deviations from the study design approved by the ethics committee.

#### Plans for communicating important protocol amendments to relevant parties (e.g., trial participants, ethical committees) {25}

Before making any changes to the study protocol, approval from the Vilnius University Research Ethics Committee must be obtained. If approved, the changes must be reported in the trial register and included in the final report of research data.

#### Dissemination plans {31a}

The results of the trial will be published in a peer-reviewed journal and presented at scientific conferences. A popular science paper will be created for wider dissemination. To engage with the public, a public event will be organized to present the results. After the publication of the trial results, anonymized dataset will be available from PI upon reasonable request.

## Discussion

Internet-delivered psychological interventions for tinnitus provide several benefits including convenience, flexibility, reduced stigma, cost-effectiveness, and potential for scalability. Offering multiple effective options for Internet-delivered psychological treatments can improve access to care and lead to better outcomes for individuals with tinnitus. More specifically, by providing a wider range of choices to better fit individual preferences, different approaches to target specific needs, easier access to care especially for those in remote areas, and ultimately, better outcomes. These factors can improve the overall quality of life for people with tinnitus. Moreover, empowering individuals to choose between multiple options can increase engagement in treatment, improve the sense of control, and enhance adherence to treatment, leading to better outcomes. The findings of this study could add to the empirical evidence of the efficacy of CBT and mindfulness-based interventions.

Overall, Internet-delivered psychological interventions might provide an accessible, flexible, and convenient way to receive evidence-based treatment for tinnitus.

## Trial status

Protocol version 1, 2022–11-13. Recruitment did not yet commence. Recruitment is planned to begin mid-February 2023 and extend into the first half of March 2023.

## Data Availability

After the publication of trial results, a de-identified dataset will be available from the PI upon a reasonable request.

## Abbreviations

CBT: Cognitive behavioral therapy
CONSORT: Consolidated Standards of Reporting Trials
ICBT: Internet-delivered cognitive behavioral therapy
iMBTSR: Internet-delivered mindfulness-based tinnitus stress reduction
ITT: Intention-to-treat
PI: Principal investigator
PPA: Per-protocol analysis
RCT: Randomized controlled trial
